### Multilevel model

We will use multilevel statistical modeling to examine parent, navigator, organizational, and state policy factors that predict implementation success (Table 2). Success will be defined as fidelity to the intervention model. Navigator fidelity will be the primary outcome as it a critical component of implementing any intervention, and the most commonly measured implementation metric [32]. We will measure fidelity at the completion of the navigator protocol. Fidelity will be defined as: 1) completion of the three home visits; 2) completion of Navigator log; and 3) adherence to the eight constructs of motivational interviewing expected to be performed by the navigators.

**Table 2 Tab2:** Measures for Multi-level Model of Navigator Fidelity

Measure	Tools	Level
Provider Density	Publically available data on certified ASD providers	State
Diagnostic Availability	Publically available data on number of ASD diagnostic centers	State
Characteristics	Organization location, size, and type	Organizational
Organizational Readiness to Change	Organizational Readiness to Change Assessment tool [52]	Organizational
Demographics	Age, race, ethnicity, gender, education, language proficiency	Navigator
Experience with ASD	Question developed by study team	Navigator
Cultural competency	Dogra’s Cultural Awareness Questionnaire [53]	Navigator
Navigator proficiency	Measure developed from Navigator training manual	Navigator
Demographics	Age, race, ethnicity, child’s gender, comorbid conditions, parental education, nativity, English proficiency, access to transportation, insurance	Parent
Parental social support	MOS-Social Support Survey [54]	Parent
Global perceived stress	Perceived Stress Scale- Self Report 14 item [55]	Parent
Parenting stress	Parenting Stress Index 4th edition – Short Form [56]	Parent
Physical/emotional health	Veterans RAND 12 Item Health Survey [57]	Parent
Parental coping strategies	Brief COPE [58]	Parent
Child’s impact on the family	Family Impact Questionnaire [59]	Parent
Parenting stress from ASD	Autism Parenting Stress Index [60]	Parent
Parental perceived mastery	Pearlin Mastery Scale [61]	Parent
Child’s adaptive functioning	Adaptive Behavior Assessment System II [62]	Parent

We will combine three data sets: parent-reported measures collected at three time points throughout the study; primary surveys of navigator and clinic data collected in year one (clinic) and three (navigator) of the project; and publically available state-level data.

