First, we will evaluate bivariate associations between parent, navigator, organizational, and state-level predictors and navigation model fidelity using χ2 test for pairs of categorical variables and 1-way ANOVA for comparing continuous and categorical variables. Since the data has a 4-level structure, with many individual families nested within navigators, navigators nested within organizations, and organizations nested within states, multilevel logistic regression will be used to account for the lack of independence. We will calculate the intraclass correlation in a null model to analyze how much of the variance in our outcome can be potentially attributed to the predictor level. This will be followed by a series of models: model #1 will examine the unadjusted association between state resources and outcomes, model #2 will add organizational characteristics to model #1; model #3 will add to model #2 by adjusting for navigator level characteristics; model #4 will further adjust model #3 for parent characteristics, and finally, model #5 will add to model #4 by adjusting for parent-reported measures.

In our sample of three states, we propose to evaluate data from 12 clinics, 8 patient navigators and 125 parents. To account for the clustered design, our estimation of power was adjusted via a design effect using an estimate of within subject correlation of the outcome parameter. A proportion of non-fidelity at the mean of 20% compared to a proportion of 0.10 at 1 SD above the mean for the predictor will yield an odds ratio of 0.44. Assuming the design effect will be no larger than 1.41 (the square root of 2), the statistical power should be computed based on a sample size of 89 for an observed sample of 125 parents. For 89 parents, the above-noted difference with an odds ratio of 0.44 will have 82% power with a two-sided alpha of 0.05.

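### The first step of aim 3 tests navigator-, organization- and state-level predictors as if the 125 families were independent; at the plan's own design-effect ceiling, a nominal 5% test has a true size of up to about 10–12%

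*Protocol article*

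**What the plan says.** The point concerns the Multilevel model section of the protocol article (under Implementation evaluation) and its Table 2.

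- **Scope of the first step:** "we will evaluate bivariate associations between parent, navigator, organizational, and state-level predictors and navigation model fidelity". Predictors at all four levels are included.
- **Tests named:** "using χ2 test for pairs of categorical variables and 1-way ANOVA for comparing continuous and categorical variables". No adjustment for clustering is stated for this step.
- **Structure of the data:** the section describes four levels, "with many individual families nested within navigators, navigators nested within organizations, and organizations nested within states", and assigns the correction to the next step: "multilevel logistic regression will be used to account for the lack of independence". A null-model intraclass correlation and models #1 to #5 follow. Each later model adds a further block of predictors.
- **Numbers of units:** "In our sample of three states, we propose to evaluate data from 12 clinics, 8 patient navigators and 125 parents".
- **Allowance for clustering in the power statement:** "Assuming the design effect will be no larger than 1.41 (the square root of 2"), from which "the statistical power should be computed based on a sample size of 89 for an observed sample of 125 parents".
- **Predictors above family level:** Table 2 lists two at state level (one is measured by "Publically available data on certified ASD providers"). It also lists organizational location, size, type and readiness to change, six navigator demographic items, and navigator ASD experience, cultural competency and proficiency.

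**The concern.** A navigator's education takes one value for all families served by that navigator, and provider density takes one value for a whole state. The information on such a predictor comes from the number of navigators, clinics or states, not from the number of families. Chi-square and one-way ANOVA on families use a variance that ignores this. If fidelity varies between navigators, clinics or states for reasons unrelated to the predictor, that variance is too small and so are the p-values.

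The section is inconsistent on this. It shrinks 125 families to 89 when it computes power, but tests the first-step associations as though no shrinkage were needed.

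Aim 3 is meant to identify what predicts implementation success, and the Discussion expects the results to inform dissemination. At stake is whether a navigator trait or clinic type is reported as related to fidelity when the data show only that navigators or clinics differ. Family-level predictors are affected only as far as they themselves cluster within navigators, clinics or states.

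**Working it through.** **Inputs from the plan:** 125 families, 8 navigators, 12 clinics, 3 states; design effect at most 1.41; non-fidelity 20% at the predictor mean and 10% one SD above it; two-sided alpha 0.05. The alpha is given in the power statement. I take it as the nominal level of the first step too, because no other is stated.

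**1. The plan's own figures.**
- Odds ratio: (0.10/0.90)/(0.20/0.80) = 0.444. The plan gives 0.44.
- Effective sample: 125/1.41 = 88.7, or 89 as stated.
- Power with 89 families and a normally distributed predictor: 83.5% by simulated Wald test, against the stated 82%. Closed-form approximations range from 70% to 86%.

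The plan therefore does apply 1.41 as a variance inflation on the number of families.

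**2. True size of an unadjusted test at that ceiling.** For a predictor constant within clusters and unrelated to fidelity, the unadjusted statistic is inflated by the design effect, so

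size = P(χ²_df > critical value / design effect).

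- 1 df (two-group predictor, or a continuous predictor compared by fidelity yes/no): 2 × [1 − Φ(1.96/√1.41)] = 2 × [1 − Φ(1.651)] = 9.9%.
- 2 df (three categories, such as state): P(χ²₂ > 5.991/1.41) = exp(−2.124) = 11.9%.

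Beta-binomial simulation with 20% non-fidelity and no true association agrees:
- two-group and continuous predictors: 9.7% to 10.2% across navigator, clinic and state level;
- three states as categories: 12.2%;
- intraclass correlation set to zero: about 5%.

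**3. What 1.41 implies at each level.** With design effect = 1 + (m − 1) × ICC, the implied ICC is 0.41/(m − 1):
- state, m = 125/3 = 41.7: ICC 0.010;
- navigator, m = 125/8 = 15.6: ICC 0.028;
- clinic, m = 125/12 = 10.4: ICC 0.044.

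The plan does not say to which level 1.41 refers. The 9.9% and 11.9% depend only on the design effect, so they hold for whichever level it describes.

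**4. Range under assumed ICCs.** The plan gives no ICC, so these values are assumptions. Entries are the design effect and the true size of a nominal 5%, 1-df test.

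| Level of predictor | ICC 0.01 | ICC 0.05 | ICC 0.10 |
|---|---|---|---|
| Clinic | 1.09, 6.1% | 1.47, 10.6% | 1.94, 16.0% |
| Navigator | 1.15, 6.7% | 1.73, 13.6% | 2.46, 21.2% |
| State | 1.41, 9.8% | 3.03, 26.0% | 5.07, 38.4% |

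Every entry for ICC 0.05 or 0.10 has a design effect above the plan's ceiling.

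**5. In counts.** Table 2 lists 4 organizational and 9 navigator predictors, counting location, size, type and each demographic item separately. If none were related to fidelity and each had a 1-df test at the ceiling, the expected number of false associations would be 13 × 0.099 = 1.3, against 13 × 0.05 = 0.65 at the nominal level.

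**The case against.** The best defence is that the first step is preliminary. The section recognizes the clustering, hands it to multilevel logistic regression, and sets out a null model and five further models. It never says that bivariate p-values choose the predictors or serve as the conclusion of aim 3. The aim is an implementation evaluation, separate from the effectiveness comparison. And 1.41 is an upper limit, so 9.9% and 11.9% are upper limits too.

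Most of this stands, and it rules out three stronger readings that a reader might infer:

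- **That false-positive rates run up to 26%.** This needs a state-level ICC of 0.05 and a design effect of about 3.03, which is more than twice the plan's ceiling. It also concerns the one level for which model #1 gives an unadjusted analysis within the multilevel series.
- **That the tests address the wrong null, namely no difference between any clusters.** That is literally so only when each cluster is its own category, as with three states. For a two-group or continuous predictor the null is still no association, and the fault is an understated variance.
- **That aim 3's models or conclusions are contaminated.** No selection rule links the first step to models #1 to #5.

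The defence does not remove the point. The article names both the tests and the levels they apply to, so this is not a detail left to another document. Nor do the later models repeat the one-predictor question for navigators and organizations. Organizational predictors enter in model #2 on top of state, and navigator predictors in model #3 on top of both. Block entry would in principle give each predictor an adjusted coefficient. But if all nine listed navigator characteristics enter together, 8 navigators supply only 7 independent contrasts and cannot separate them. Readers would then be likely to turn to the first-step results.

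**Conclusion.** The point holds in limited form. The first-step chi-square and ANOVA p-values are too small for predictors above family level, and the section's own statements on clustering show why. On the plan's figures the true size of a nominal 5% test is at most about 10% with one degree of freedom and about 12% with three categories. This assumes that the 1.41 ceiling applies at the level where the predictor varies, that clusters are of roughly equal size, and that the first step uses the 5% level. Any larger figure for such tests rests on an ICC that the plan does not give.

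The consequence is misleading first-step associations, chiefly for navigator and organizational predictors. The multilevel models and the trial's effectiveness analyses are not affected. The change should be made, but it concerns a preliminary step of an implementation aim.

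**What to change.** For navigator and organizational predictors, replace chi-square and ANOVA with one of the following:

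- a one-predictor multilevel logistic model with a random intercept at the level where the predictor varies and a small-sample correction, since there are only 8 navigators and 12 clinics;
- a test at cluster level, for example a permutation of navigator or clinic labels on the cluster fidelity proportions;
- a descriptive presentation of this step, without p-values.

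With only three states, present state-level associations descriptively whichever option is chosen. The same one-predictor multilevel model can serve for family-level predictors, where it guards against any clustering in the predictor itself.

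This changes analysis wording only, with no new data and no change to recruitment. The downside is fewer nominally significant predictors and wider intervals, which reflects what 8 navigators and 12 clinics can support.

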**Methods:**

This study uses a hybrid type I randomized effectiveness/implementation design to test effectiveness and collect data on implementation concurrently. It is a two-arm comparative effectiveness trial with a target of 125 participants per arm. Participants are families of children age 15–27 months who receive a positive screen for ASD at a primary care visit at urban clinics in Massachusetts (*n* = 6 clinics), Connecticut (*n* = 1), and Pennsylvania (*n* = 2). The trial measures diagnostic interval (number of days from positive screen to diagnostic determination) and time to receipt of evidence-based ASD services/recommended services (number of days from date of diagnosis to receipt of services) in those with PN compared to and activated control -Conventional Care Management – which is similar to care management received in a high quality medical home. At the same time, a mixed-method implementation evaluation is being carried out.

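### The implementation model asks more of 3 states, 8 navigators and about 25 events than they can give, and its 82% power covers only a family-level predictor

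*Protocol article*

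**What the plan says.** The Multilevel model section of the protocol article describes the data as having "many individual families nested within navigators, navigators nested within organizations, and organizations nested within states", and chooses multilevel logistic regression to handle the dependence. The sample is given as three states, and "we propose to evaluate data from 12 clinics, 8 patient navigators and 125 parents". The abstract counts clinics differently: six in Massachusetts, one in Connecticut and two in Pennsylvania.

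Table 2 assigns each measure to the state, organizational, navigator or parent level. After bivariate chi-square and one-way ANOVA tests and a null model for the intraclass correlation (ICC), five cumulative models follow. They start with state resources and add organizational, navigator, parent and parent-reported blocks in turn.

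The power statement takes "A proportion of non-fidelity at the mean of 20" per cent, against 0.10 one standard deviation higher on the predictor. The clustering allowance reads "Assuming the design effect will be no larger than 1.41 (the square root of 2", which turns 125 parents into an effective 89 and gives 82% power at two-sided 0.05. No ICC value is printed.

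**The concern.** The aim is to learn which state, organizational, navigator and parent factors predict implementation success. The first three kinds of factor vary only between states, clinics or navigators, and there are very few of each. If the predictors at a level outnumber its units, their coefficients are not determined by the data, however many families are enrolled. If the power statement counts families, it says nothing about factors that take only 3 or 8 distinct values.

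At stake is the only quantitative analysis of what drives fidelity. Run as written, it would stop at the third model or be cut down by choices made after seeing the data. The unclustered bivariate tests might then become the evidence that readers rely on.

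**Working it through.** **Inputs.** From Multilevel model: 3 states, 12 clinics, 8 navigators, 125 parents; non-fidelity 0.20 and 0.10; design effect 1.41. From the abstract: 6 + 1 + 2 = 9 clinics. From Table 2, counting each listed item once: 2 state, 4 organizational (location, size, type, readiness), 9 navigator (six demographics, autism experience, cultural competency, proficiency), 10 parent characteristics and 9 parent scales.

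**1. The plan's own power figure.**
- Odds ratio = (0.10/0.90) / (0.20/0.80) = 0.444.
- Effective n = 125/1.41 = 88.7, rounded to 89.
- Simulated power of a two-sided Wald test for one continuous predictor at n = 89: about 83%. The stated 82% reproduces. Closed-form approximations scatter around it, from 70% to 86%.

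**2. Nesting.** If each navigator belongs to one clinic, 8 navigators reach at most 8 clinics, which leaves at least 4 of 12 (or 1 of 9) without one. So some navigators must cross clinics. If organization is read as the three care networks in Setting, each network lies in one state and the organizational and state levels are the same three units. The data sources described in Multilevel model also point to clinics as the organizational unit.

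**3. Estimability.**
- State level: intercept + 2 predictors = 3 parameters for 3 states. Nothing is left for a between-state variance.
- Navigator level: intercept + 9 predictors = 10 columns, each constant within navigator. With 8 navigators the rank is at most 8.
- Model #3 in full: 1 + 2 + 4 + 9 = 16 columns. The rank is 8 under strict nesting, and 14 in a worked example with navigators crossing clinics. It is deficient either way, and models #4 and #5 inherit this.

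**4. Events per predictor.** Predictors in model #5: 2 + 4 + 9 + 10 + 9 = 34, before dummy variables or subscales. Events: 0.20 × 125 = 25 (about 28 if 20% holds only at the predictor mean). Ratio: 25/34 = 0.74.

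**5. Where the 82% applies.** No ICC is given, so the ICCs below are assumptions. Families per navigator: m = 125/8 = 15.6.
- *Family-level predictor.* The variance factor is roughly 1 + (m − 1) × ICC of predictor × ICC of outcome. With both at 0.10: 1 + 14.6 × 0.01 = 1.15, below 1.41. Simulated unadjusted power with 125 families is about 90–94%, with type I error of about 4–5%. With ICCs taken on the observed scale instead, power is about 85–92%. The stated 82% is therefore on the cautious side here.
- *Cluster-level predictor.* Keep 1.41, and use a t reference with (units − 2) degrees of freedom and noncentrality √(88.7 × 0.20 × 0.80) × |ln 0.444| = 3.77 × 0.811 = 3.05. The same formula with a normal reference gives 86%. With the t reference:

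| Predictor level | Units | df | Power |
|---|---|---|---|
| Clinic | 12 | 10 | 79% |
| Clinic | 9 | 7 | 75% |
| Navigator | 8 | 6 | 72% |
| State | 3 | 1 | 19% |

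These values still grant the design effect of 1.41. For a navigator-level predictor that needs an ICC of no more than 0.41/14.6 = 0.028.

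**6. Bivariate tests.** For a navigator-level predictor with no effect, a logistic test that treats the 125 families as independent rejects in about 7–14% of simulations at logit-scale ICCs of 0.03–0.10, against a nominal 5%. This stands in for the planned chi-square and ANOVA tests, which ignore clustering in the same way.

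**The case against.** Several points on the other side stand.

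- Table 2 is a list of measures. Coding and selection could be settled in an analysis plan not shown here, and merging items would lower the count of 34. But the article itself fixes the blocks, their order and the unit counts. Reducing nine navigator items to seven would restore rank and still leave no residual at that level.
- The null model and models #1 and #2 can be run. It would be too strong to say that nothing in the sequence can be fitted; the rank failure starts at model #3. In the earlier models the problem is a between-state variance that cannot be meaningfully estimated.
- A reader might infer that the square root of 2 is really a standard-error factor, so that the design effect should be 2 and the effective sample 62.5. The article calls 1.41 the design effect and uses it consistently as one. The other reading is a guess about intent.
- A reader might also divide 125 by 1 + (m − 1) × ICC and conclude that power is far below 82% for every predictor. That factor belongs to predictors constant within a cluster. For a family-level predictor it overstates the loss, as step 5 shows.
- Nine and 12 clinics may both be right: nine primary care clinics plus the three networks' autism specialty clinics make 12. The article does not say so, and a clarification is enough.
- No significance level or selection rule is attached to the bivariate step, multilevel models follow it, and inflation is negligible for parent-level measures. The warning is confined to state, clinic and navigator predictors.
- The article frames its implementation framework as suited to formative work, and the randomized effectiveness comparison is separate. Both limit how serious this is.

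**Conclusion.** The point holds for the implementation aim only. From printed counts alone, the nesting is not possible with every clinic served, models #3 to #5 are rank-deficient as listed, and the state level is saturated. Model #5 would have about 0.7 events per predictor. That ratio rests on counting each Table 2 item once and on the 20% non-fidelity rate. The rate in turn depends on how fidelity is defined: 32 components in Implementation evaluation, three criteria in Multilevel model.

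The 82% power is not an arithmetic error. It is a reasonable, even cautious, figure for one unadjusted family-level predictor, but it does not describe state, clinic or navigator predictors, which have 3, 9–12 and 8 independent units. The 7–14% type I error depends on assumed ICCs and on a navigator-level predictor. This should be corrected before the implementation analysis, but it gives no reason to doubt the trial's primary comparison.

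**What to change.** Rewrite the analysis and power paragraphs of Multilevel model:

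1. Replace the four-level nesting with state (network) as a fixed effect and a random intercept for navigator, crossed with clinic if navigators serve several.
2. Limit inferential predictors to a few named family-level baseline measures, in keeping with about 25 events.
3. Report state, clinic and navigator factors descriptively, beside the process mapping and interviews, without p-values from the unclustered bivariate tests.
4. State that the 82% power applies to a single unadjusted family-level predictor.
5. Reconcile the clinic count (9 or 12) and say what counts as an organization.

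The change is to wording only and needs no new data. The cost is that state, clinic and navigator factors are no longer formally tested, which 3 states, 9–12 clinics and 8 navigators could not support in any case.

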## Discussion

The current study is advances the field of ASD services for multiple reasons. First, it is the first large randomized trial of an intervention specifically designed to improve utilization of evidence-based care for children with ASD. Children with ASD experience significant delays in care, and many engage in alternative, or non-evidence based practice [40]. If proven effective, future work may consider prolonging the intervention to continue to assure appropriate utilization of EBS for this children beyond the initial diagnostic period.

Second, we are testing an intervention designed to alleviate disparities. Addressing disparities is particularly important for children with ASD, who experience significant differences in utilization of EBS based on racial, ethnic, and socioeconomic status [41–44]. Minority families of children with ASD may be particularly vulnerable to disparities in service engagement. For example, a diagnosis of ASD is considered stigmatizing in certain cultures [10], and a fear of stigma may create barriers to both obtaining a diagnosis and engagement in services [45]. Moreover, compared to many other neurodevelopmental conditions, ASD services require intensive parent involvement and training. [46] These requirements may be difficult for families who lack financial resources, support networks, are non-English speaking, or who have other competing demands. Multiple studies show that cultural attitudes towards child development and developmental disabilities shape how minority families respond to the challenges of ASD [45, 47]. studies show Latina mothers to have limited knowledge about autism, and often have differing views of their children’s developmental and the importance of treatment services compared to their medical providers [48]. In their study of South Asian immigrant families [45], Jegatheesan et al. report a perceived gap between service providers’ and families’ views of the child’s home. Whereas providers viewed the home as a stable, closed environment, families emphasized the importance of flexibility and openness to relatives and community members. They observed that differing perspectives resulted in families withdrawing from services. Taken together, these data suggest that testing a family-focused, culturally sensitive intervention designed to address disparities is particularly important in this population.

Finally, given the hybrid effectiveness/implementation design, at the end of the study, we will both know if PN is effective, and have collected data that can inform the rapid, large-scale dissemination of PN for vulnerable children with ASD. These data may also be applicable to those working to disseminate other systems-based strategies designed to improve access to services for children at risk for ASD or other mental health or developmental disorders [24]. Finally, we anticipate these data will provide insight to investigators, community organizations, or states working to implement PN interventions for both ASD and other common disorders that experience disparities in care such as asthma or HIV [15, 49].

